### Withdrawal of Subjects

Parents and caregivers can withdraw consent at any time and for any reason if they wish to do so without any consequences. All withdrawn infants will receive regular treatment as usual.

### (Serious) Adverse Events

Adverse events are defined as any undesirable experience related to PBCC occurring to a subject during the study. All adverse events observed by the researcher or the staff will be recorded and reported to the IRB.

This study population has a high risk of serious complications (so-called “context-specific serious adverse events (SAEs)”), which are inherent to their vulnerable condition and unrelated to the intervention which is under evaluation in this trial. These complications are included in the secondary outcomes of this study and are recorded in the Case Report Form. Yearly, an overview of the context-specific SAEs for each treatment arm will be presented to the IRB.

Stabilization of preterm infants with the resuscitation table as close as possible to the mother has been performed before and is considered safe. The present study uses a similar approach, using the following modifications: (1) stretching of the umbilical cord is prevented, (2) full standard care for stabilization can be provided, and (3) extended infant monitoring is included. We do not expect that PBCC poses extra risks to standard stabilization of the preterm infant. Nevertheless, we have included several “safety parameters” as secondary outcomes. The two most important safety parameters are maternal blood loss and admission temperature of the infant at the NICU.

This is a small trial where only 32 infants will be included in each group and a Data Safety Monitoring Committee will not be installed. All SAEs mentioned above will be recorded in the Case Report Form. All SAEs will be reported to the IRB. Any unforeseen SAEs that was life threatening or resulted in death and was directly related to the PBCC approach will be reported without undue delay after obtaining knowledge of the event.

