### Sample Size Calculation

There is no data available concerning the effectiveness of stabilization during PBCC and comparing PBCC with standard approaches. Few studies have performed initial respiratory support before cord clamping, but all of them used predefined timing of cord clamping, varying from 30 to 120 s. Data from our feasibility study showed a median time to obtain respiratory stability of 4:23 min [IQR 3:00–5:11] when PBCC is performed.

Using the routine approach the mean time needed to stabilize an infant, starting from birth, is 5 ± 2 min (unpublished data, Leiden database). If there is truly no difference for the time needed to stabilize an infant between the standard approach and PBCC, then 64 infants (32 in each treatment arm) are required to have 80% power to assess whether the lower limit of a one-sided 97.5% confidence interval (or equivalently a 95% two-sided confidence interval) around the difference in the mean-time to stabilization (mean time in the standard group minus mean time in the experimental treatment group) will be above the non-inferiority limit of −75 s. We have chosen the non-inferiority level of 75 s, because this difference is still acceptable according to the current clinical guidelines. We will take in consideration that 7% of infants (unpublished data, Leiden database) will not reach our primary endpoint set for stabilization, because they need continuous PPV, with or without intubation. These infants will be included in all intended analyses.

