### Statistical Analysis

Normally distributed data will be presented as means ± standard deviations, not-normally distributed data as medians and interquartile ranges. Categorical data will be analyzed using the Chi-square test. Continuous data will be analyzed using the Student's *t*-test or Mann-Whitney test as appropriate. Intention-to-treat analysis and per-protocol analysis will be performed. The effect of PBCC on the primary outcome will be assessed by multi-variable logistic regression analysis including possible confounders.

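### Admission temperature, ranked as a lead safety parameter, appears in the outcome list only as a hypothermia rate, which loses information; it and maternal blood loss should be reported as differences with 95% intervals

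*Protocol article*

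**What the plan says.** Three places in the protocol article bear on this.

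- *(Serious) Adverse Events* gives the investigators' expectation, "We do not expect that PBCC poses extra risks to standard stabilization of the preterm infant", then says that safety parameters have nevertheless been placed among the secondary outcomes, and ranks them: "The two most important safety parameters are maternal blood loss and admission temperature of the infant at the NICU".
- *Secondary Outcomes*: the list on the infant's transition has one entry on temperature, a hypothermia rate on NICU admission. The article gives no threshold for it. The maternal list has blood loss itself and, as a separate entry, the rate of postpartum haemorrhage.
- *Statistical Analysis*: "Categorical data will be analyzed using the Chi-square test". Continuous outcomes go to a t-test or a Mann-Whitney test. Summaries are means with SD or medians with interquartile range, and no interval for a between-arm difference is mentioned.

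The only comparison framed through a confidence limit is the primary outcome, under *Sample Size Calculation*: "We have chosen the non-inferiority level of 75 s".

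**The concern.** The safety section and the outcome list do not name the same variable. One ranks admission temperature; the other lists a yes/no rate derived from it. Read literally, the outcome list and the analysis section together send a lead safety parameter to a Chi-square test on two proportions. The temperature has to be measured to classify an infant as hypothermic, so the finer value is available at no cost and would go unused. In a trial of this size the loss matters.

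The form of the result matters as well. A p-value from a test of zero difference does not tell the reader how large a harm is still compatible with the data, which is what one wants to know about a safety parameter. A between-arm difference with its interval does. The plan already reasons this way for the primary outcome.

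**Working it through.** **Planned size.** The protocol says "then 64 infants (32 in each treatment arm) are required to have 80% power". That figure belongs to the primary outcome; no power or precision is stated for any safety parameter. For context, take the SD from "the mean time needed to stabilize an infant, starting from birth, is 5 ± 2 min" (2 min = 120 s), a margin of 75 s and a true difference of 0:

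n per arm = 2 × [(z₁₋α + z₀.₈₀) × 120/75]²

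- one-sided 0.025: 2 × [(1.960 + 0.842) × 1.6]² = 40.2, so 41 per arm (82 in all)
- one-sided 0.05: 2 × [(1.645 + 0.842) × 1.6]² = 31.7, so 32 per arm (64 in all)

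The stated 64 therefore corresponds to a one-sided 5% level, not to the stated one-sided 97.5% interval. That is a separate matter. Below, 32 per arm is taken as the planned number.

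**Inputs for the safety check.** From the document: 32 per arm, and Chi-square for a rate or t-test for a continuous value. Assumed, because the document does not give them: two-sided 5% for secondary outcomes; normally distributed temperature with equal SD in both arms; a downward shift of 0.5 SD; control hypothermia rates of 20%, 30% and 50%.

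**Continuous temperature.** Noncentrality = 0.5 / √(2/32) = 0.5 / 0.25 = 2.0, with 62 degrees of freedom and critical value t(0.975, 62) = 1.999. Power from the noncentral t distribution is 0.504, so the shift is missed about 50% of the time.

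**The same shift seen as a rate.** If a fraction p of control infants lies below the cut-off, a 0.5-SD shift puts p₂ = Φ(Φ⁻¹(p) + 0.5) below it. Power is by exact enumeration of the uncorrected Chi-square test at 32 v 32.

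| Control rate (assumed) | Rate after shift | Power, rate | Power, continuous |
|---|---|---|---|
| 20% | Φ(−0.842 + 0.5) = 36.6% | 0.32 | 0.50 |
| 30% | Φ(−0.524 + 0.5) = 49.0% | 0.36 | 0.50 |
| 50% | Φ(0 + 0.5) = 69.1% | 0.37 | 0.50 |

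**Range over the assumed shift.** The same two methods give:

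| Shift | Power, rate (control 20–50%) | Power, continuous |
|---|---|---|
| 0.4 SD | 0.22–0.26 | 0.35 |
| 0.5 SD | 0.32–0.37 | 0.50 |
| 0.6 SD | 0.44–0.49 | 0.66 |
| 0.7 SD | 0.56–0.62 | 0.79 |

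The level of power depends strongly on the assumed shift. The ordering does not: the continuous value does better in every row.

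**Precision of a difference.** The half-width of the 95% interval for a continuous outcome is t(0.975, 62) × √(2/32) = 1.999 × 0.25 = 0.50 SD. With an observed difference of exactly zero, the interval would still reach 0.50 SD on the unfavourable side. For a rate, the half-width is 1.96 × √(2p(1−p)/32): 19.6 percentage points at p = 20%, 22.5 at 30% and 24.5 at 50%.

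**Unit for blood loss.** Blood loss belongs to the mother. Under *Randomization, Blinding and Treatment Allocation*, vaginally delivered twins share an arm, so two infants bring one mother. With caesarean twins the first infant gets standard treatment and the second is randomized, so one mother can fall in both arms. Twins can thus leave fewer than 32 independent mothers per arm, and 0.50 SD is then the best case for blood loss.

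**The case against.** The strongest reply is that this is a condensed article on a small trial of how effectively infants are stabilized. Low power on secondary safety outcomes is expected, and the protocol itself calls the trial small. Intervals and any pre-set safety limit may be in the full protocol or SAP, which are not shown. The safety section does name admission temperature among the secondary outcomes, and the continuous-data tests would cover it, so the gap could be a slip of wording in a shortened list. An interval also rests on the same 32 per arm and adds no information.

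Much of this stands. The absence of a safety limit is not a fault that can be charged to this document, and low power alone is not an error. What remains is that two sections describe one lead safety parameter differently, and that the listed version is the weaker one. The interval does not add data, but it shows openly what a p-value hides.

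Some stronger readings are tempting and are not supported.

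- A reader might infer that a non-significant safety test is planned as evidence of no added risk. The protocol states an expectation beforehand and gives no rule for reading a null result.
- A reader might infer that these tests open the way to the large trial. The Discussion makes that step depend on time to stabilization, and says that feasibility and safety were assessed in an earlier study.
- A reader might infer that safety is judged by these tests alone. Adverse events and SAEs also go to the IRB, with a yearly overview by arm of the context-specific SAEs.
- A reader might take a fixed miss rate for a relevant harm as established. The document does not say what size of harm is relevant.

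**Conclusion.** The point holds in a limited form. The protocol ranks admission temperature as a lead safety parameter but lists it only as a hypothermia rate. Under the assumptions of a 0.5-SD shift, control rates of 20–50%, normal temperatures, 32 per arm and two-sided 5%, that choice lowers power from about 50% to about 32–37%. The absolute figures move with the assumed shift, but the loss is there throughout the range examined. Maternal blood loss is already listed as such. For it, the point is only that a difference with an interval says more than a test, and that the number of mothers may be below the number of infants. This is a worthwhile improvement in the outcome list and in reporting; it does not show that the trial's safety assessment is invalid.

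**What to change.** In the secondary outcomes on the infant's transition, list admission temperature in °C as a continuous outcome and keep the hypothermia rate beside it.

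In *Statistical Analysis*, add that admission temperature and maternal blood loss are each reported as a between-arm difference with a two-sided 95% confidence interval, and that any statement on safety rests on the interval. State that blood loss is analysed per mother, and how mothers of caesarean twins with one infant in each arm are handled.

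This is wording only: no further infants and no further measurements. The small downside is that, with a half-width of about 0.50 SD, the report will probably have to say that a moderate harm is not excluded.

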### Statistical Analysis

Normally distributed data will be presented as means ± standard deviations, not-normally distributed data as medians and interquartile ranges. Categorical data will be analyzed using the Chi-square test. Continuous data will be analyzed using the Student's *t*-test or Mann-Whitney test as appropriate. Intention-to-treat analysis and per-protocol analysis will be performed. The effect of PBCC on the primary outcome will be assessed by multi-variable logistic regression analysis including possible confounders.

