### Primary Outcome

The primary outcome will be the time needed to stabilize the infant, starting from birth. Stable is defined as the establishment of regular spontaneous breathing, a heart rate ≥ 100 bpm and oxygen saturation above 90% while using FiO2 < 0.40.

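### The model named for the primary outcome is logistic regression, whose odds ratio cannot be set against the −75 s margin on the difference in mean time

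*Protocol article*

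**What the plan says.** The Primary Outcome section defines a duration: "The primary outcome will be the time needed to stabilize the infant, starting from birth".

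The Sample Size Calculation section fixes the decision rule. The effect measure is "mean time in the standard group minus mean time in the experimental treatment group". The criterion is that the "lower limit of a one-sided 97.5% confidence interval (or equivalently a 95% two-sided confidence interval") "around the difference in the mean-time to stabilization" "will be above the non-inferiority limit of −75 s". The same section expects 7% of infants never to reach the endpoint and keeps them in every intended analysis.

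The Statistical Analysis section has one sentence that names the primary outcome: "The effect of PBCC on the primary outcome will be assessed by multi-variable logistic regression analysis including possible confounders". For continuous variables in general it says: "Continuous data will be analyzed using the Student's *t*-test or Mann-Whitney test as appropriate". It does not link either test to the primary outcome or to the margin.

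The only binary form of the outcome is failure to reach stability within 10 minutes, and it is listed among the secondary outcomes on the infant's transition.

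**The concern.** The method assigned to the primary outcome does not fit the outcome or the rule for judging it. A logistic model can be fitted only after the time has been cut into two classes. Its result is then a ratio of odds, which cannot be placed above or below a limit expressed in seconds. Choosing a cut would change the question from how much longer stabilization takes on average to whether it is complete by a chosen moment. It would also discard information.

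The Discussion makes the large multicentre trial conditional on this hypothesis being confirmed. The trial is also unblinded. The analysis that decides it should therefore be fixed without ambiguity, and should not be settled between a logistic model, a t-test and a rank test once the data are in.

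**Working it through.** **1. The three statements side by side**

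| Element | Section | Content | Scale |
|---|---|---|---|
| Outcome | Primary Outcome | time from birth to stability | time |
| Decision rule | Sample Size Calculation | 95% CI for difference in means, standard minus PBCC, against −75 s | seconds |
| Model | Statistical Analysis | multivariable logistic regression | log odds, no unit |

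The first two agree. The third agrees with neither, and the article supplies no cut-point or odds-ratio margin to connect them.

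**2. The plan's own figure**

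The plan states: "then 64 infants (32 in each treatment arm) are required to have 80% power". Inputs from the Sample Size Calculation section are SD 2 min = 120 s, margin 75 s and true difference 0. The formula is n per arm = 2(z₁₋α + z₀.₈₀)² × (SD/margin)².

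- One-sided 2.5%, as stated: 2 × (1.960 + 0.842)² × (120/75)² = 40.2, so 41 per arm and 82 in total.
- One-sided 5%: 2 × (1.645 + 0.842)² × 2.56 = 31.7, so 32 per arm and 64 in total.

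The 64 is reproduced only at one-sided 5%. That is a separate matter. For this point, what counts is that the sample size was derived for a difference in means, not for an odds ratio.

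**3. What a mean-difference analysis delivers**

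With 32 per arm, SD 120 s and no covariates, the 95% half-width is 1.960 × 120 × √(2/32) = 58.8 s (60.0 s with the t quantile). This is in seconds and can be read directly against −75 s. Power when the arms are truly equal is about 70.5% at one-sided 2.5% (normal approximation).

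**4. What a logistic analysis would deliver (illustration)**

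This step assumes normal times with SD 120 s, mean 300 s under standard care, and mean 300 + 75 = 375 s for PBCC at the margin. The proportions stable by cut c are p₀ = Φ((c − 300)/120) and p₁ = Φ((c − 375)/120). The implied margin is OR = [p₁/(1 − p₁)]/[p₀/(1 − p₀)]. Non-inferiority power with equal arms is Φ(|ln OR|/SE − 1.960), with SE = √(2/(32 p₀(1 − p₀))).

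| Cut | p₀ | p₁ | OR at 75 s | Power |
|---|---|---|---|---|
| 4 min | 0.309 | 0.130 | 0.34 | 52% |
| 5 min | 0.500 | 0.266 | 0.36 | 53% |
| 6 min | 0.691 | 0.450 | 0.37 | 46% |
| 7 min | 0.841 | 0.646 | 0.34 | 34% |
| 8 min | 0.933 | 0.809 | 0.30 | 22% |
| 10 min | 0.994 | 0.970 | 0.20 | 7% |

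The implied odds ratio depends on the cut and on the assumed distribution. Power is below that of the mean comparison at every cut. The model places only 0.6% of standard-care infants beyond 10 minutes and ignores the expected 7% who never stabilize, so the last row is the least secure.

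**The case against.** The strongest reply is that the trial already has a usable rule. The Sample Size Calculation section states the effect measure, its direction, the confidence level and the margin. The Statistical Analysis section lists the Student's t-test, which yields that difference in means with its interval. The logistic sentence, with its mention of confounders, could then be an adjusted analysis beside the main comparison.

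Much of this stands. A reader might infer that the trial has no valid route to its non-inferiority conclusion, and the article does not support that, because an unadjusted comparison with −75 s remains available. Yet the logistic analysis is not labelled secondary. It is the only method tied to the primary outcome, and the t-test is offered only as one of two options, to be chosen as appropriate. The feasibility times are given as a median with interquartile range, and 7% of infants are expected to have no stabilization time. The choice could therefore plausibly fall on Mann-Whitney.

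A rank test is not confined to superiority. It can be shifted by 75 s or inverted to a Hodges-Lehmann interval in seconds. That interval concerns a location shift, however, and not the mean difference in the stated rule. A non-significant Mann-Whitney p-value is not evidence of non-inferiority.

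A reader might also infer that the logistic model is meant for failure at 10 minutes, with 0.07 × 64 = 4.5 expected events and hence an unstable fit. The article does not support this either. The 10-minute outcome is secondary. The 7% describes infants needing continuous positive-pressure ventilation, not the proportion unstable at 10 minutes. The covariates are not named. That count is illustrative at most.

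**Conclusion.** The point holds as an inconsistency within the article: the model assigned to the primary outcome is of the wrong type for a time outcome and for a margin in seconds. This follows from the three statements alone and needs no numerical assumption. It is a stated method, not a detail left to a fuller document.

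The consequence is limited. The decision rule is intact and an unadjusted t-test could serve it, so what is wrong is the named model and the missing link between the rule and the analysis. The ranges given above (odds ratio 0.20 to 0.37, power 7% to 53% for cuts of 4 to 10 minutes) rest on normal times with mean 300 s and SD 120 s. They show only that the margin has no fixed counterpart on the odds-ratio scale.

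The sentence should be corrected before analysis, because the decision to proceed to the large trial depends on this result.

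**What to change.** In the Statistical Analysis section:

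- For the primary outcome, replace the logistic model with a linear model of time to stability, adjusted for the stratification factors (gestational-age group and centre).
- Report the adjusted mean difference, standard minus PBCC, with a two-sided 95% confidence interval. Declare non-inferiority only if the lower limit is above −75 s.
- Tie the primary conclusion to that interval and not to a Mann-Whitney p-value. A bootstrap interval for the mean difference is one option if normality is doubtful.
- State how infants who never reach stability enter the analysis. The article includes them in all analyses, but they have no observed time and the linear model cannot use them without a rule. At 7% of 64 this is about 4 or 5 infants.
- Keep logistic regression for binary secondary outcomes.

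The change costs one or two sentences plus the rule for non-stabilized infants. It needs no additional infants and no new measurements.

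### The adjusted analysis tied to the primary outcome is a logistic regression, which cannot be set against the −75 s non-inferiority limit and contradicts the outcome and decision rule stated elsewhere

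*Protocol article*

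**What the plan says.** The Primary Outcome section defines a continuous quantity: "The primary outcome will be the time needed to stabilize the infant, starting from birth".

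The Sample Size Calculation sets the decision rule. A two-sided 95% confidence interval (equivalently a one-sided 97.5% interval) is placed "around the difference in the mean-time to stabilization", defined as "mean time in the standard group minus mean time in the experimental treatment group", and non-inferiority requires that its lower limit "will be above the non-inferiority limit of −75 s". The same section expects 7% of infants not to reach the endpoint and keeps them in every intended analysis.

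The Statistical Analysis section has a general rule that does not name the primary outcome: "Continuous data will be analyzed using the Student's" *t*-test or the Mann-Whitney test. Its last sentence is the only one that names the primary outcome: "The effect of PBCC on the primary outcome will be assessed by multi-variable logistic regression analysis including possible confounders".

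The only yes/no version of stability, failure to reach it within 10 minutes of birth, is listed among the secondary outcomes on transition.

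**The concern.** A binary logistic model takes a yes/no outcome and estimates an odds ratio. The primary outcome is a time, and the limit is in seconds. Fitting the named model would mean first turning the time into a yes/no variable. The article states no cut for doing so and no odds-ratio limit to test against. An ordinal logistic model would avoid the cut, but it is not mentioned and would not give a result in seconds either.

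At stake is which result answers the trial's one non-inferiority question. The Discussion makes a large multicenter trial conditional on that answer. With an unadjusted comparison in seconds and an adjusted odds ratio both available, readers could be given two results on different scales, only one of which can be checked against −75 s. Choosing different covariates would not help, because the fault lies in the type of model.

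**Working it through.** **Passages side by side**

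| Section | Outcome type | Effect measure | Comparable with −75 s? |
|---|---|---|---|
| Primary Outcome | time from birth | none stated | not applicable |
| Sample Size Calculation | time | difference in means, 95% CI | yes |
| Statistical Analysis, general rule, t-test | continuous | difference in means | yes |
| Statistical Analysis, general rule, Mann-Whitney | continuous | rank comparison | no |
| Statistical Analysis, sentence naming the primary outcome | yes/no (or ordered) | odds ratio | no |

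**The comparison in seconds.** Inputs from the Sample Size Calculation: SD 2 min = 120 s, 32 infants per arm, true difference 0, limit 75 s, one-sided 0.025.

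- The plan's own figure is "64 infants (32 in each treatment arm) are required to have 80% power". At the stated level, n per arm = 2 × 120² × (1.960 + 0.842)² / 75² = 40.2, so 41 per arm or 82 in total. The stated 64 is reproduced at one-sided 0.05: 2 × 120² × (1.645 + 0.842)² / 75² = 31.7, so 32 per arm. That mismatch is a separate matter and is not part of this point.
- Standard error with 32 per arm: 120 × √(2/32) = 30 s.
- Power: Φ(75/30 − 1.96) = Φ(0.54) = 0.705, or 0.692 with the t distribution.

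The question is therefore well posed in seconds.

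**Can −75 s be carried over to an odds ratio?** This needs assumptions that the article does not make: normal times, mean 300 s and SD 120 s under standard care, mean 375 s at the limit, and a cut c. The odds ratio for being stable by c is [p₁/(1 − p₁)] / [p₀/(1 − p₀)], where p₀ = Φ((c − 300)/120) and p₁ = Φ((c − 375)/120).

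| Cut | p₀ | p₁ | Odds ratio for a 75 s delay |
|---|---|---|---|
| 3 min | 0.159 | 0.052 | 0.291 |
| 4 min | 0.309 | 0.130 | 0.336 |
| 5 min | 0.500 | 0.266 | 0.362 |
| 6 min | 0.691 | 0.450 | 0.365 |
| 7 min | 0.841 | 0.646 | 0.344 |
| 10 min | 0.994 | 0.970 | 0.199 |

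The implied limit changes with the cut, so −75 s does not define an odds-ratio limit unless a cut is stated.

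**What the correction must also cover.** With 7% not reaching the endpoint, 64 × 0.07 = 4.5 infants have no observed time. The value assigned to them affects a mean. If, for illustration, one such infant were entered at 600 s instead of 300 s, that arm's mean would move by 300/32 = 9.4 s.

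**The case against.** The strongest reply is that the plan already contains the right analysis. The Sample Size Calculation fixes the effect measure, the limit and the interval. The general rule sends continuous data to the t-test, whose interval is in seconds. The word logistic may be a slip for linear, or the model may be meant only as a supplementary adjusted analysis.

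Most of this stands. A reader might infer that the trial, run as written, would give no estimate in seconds and no test of its hypothesis. The documents do not support that, because the t-test route exists. What remains is that this route is generic and shares its sentence with a rank test that does not estimate a mean difference, while the sentence that names the primary outcome points to a model on another scale. Nothing in the article says that it is a slip or supplementary.

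Two further inferences should be resisted.

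- A reader might infer that a cut will be chosen after open-label data have been seen. The article proposes no dichotomisation of the primary outcome, and the full protocol and any analysis plan are not shown, so neither a cut nor its timing can be asserted.
- A reader might attach a definite power loss to the error. Such figures depend on the assumed cut and on the approximation. At 5 minutes, power is about 53% on the log-odds scale and 47% on the risk-difference scale. At 6 minutes it is 46% and 55%, and at 8 minutes about 22% and 51%. Treating the 7% as failures by 10 minutes is also an assumption, since the article attaches no time point to that figure. It conflicts with the normal model too, which puts only about 0.6% beyond 600 s.

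**Conclusion.** The contradiction is real and rests on the text alone: a time outcome with a limit in seconds is paired with a model that returns an odds ratio, and neither a cut nor an odds-ratio limit is stated. It concerns the adjusted analysis of the primary outcome, since an unadjusted interval in seconds can still be obtained. The odds-ratio range of 0.20 to 0.37 is illustrative. It assumes normal times and cuts that the protocol does not contain, and it serves only to show that −75 s has no unique counterpart on that scale. No power loss is claimed as the cost of the error. The covariate list may properly sit in an analysis plan, so its absence here is not part of the point.

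**What to change.** Replace the last sentence of the Statistical Analysis section with text along these lines:

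> The effect of PBCC on time to stability, in seconds from birth, will be estimated by linear regression on treatment group and covariates listed before outcome data are seen. The two-sided 95% confidence interval for the adjusted mean difference (standard minus PBCC) will be compared with −75 s, using a robust or bootstrap interval if the times are skewed. Infants who never reach stability will enter by one rule, fixed in advance and identical in both arms. Logistic regression will be used for yes/no secondary outcomes only.

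The text should also say whether the adjusted or the unadjusted interval decides non-inferiority.

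The rule for infants who never stabilize is a necessary part of the change. A linear model has no value for them unless one is assigned, and the Sample Size Calculation keeps them in all analyses. A robust or bootstrap interval does not solve this.

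The cost is a short text change and one decision on that rule, made before outcome data are examined. It needs no additional infants or measurements.
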